### Sample size

The sample size calculation is based on a between-group comparison of the mean change in HAM-D-17 scores from baseline to day 20. Analysis of covariance (ANCOVA) will be used, with the change in HAM-D-17 score from baseline to day 20 as the outcome and baseline HAM-D-17 score and sex as covariates. In our previous pilot study [16], involving 10 participants with moderate to severe MDD who received three FES sessions per week (ranging from a minimum of 10 to a maximum of 40 total sessions), FES demonstrated a moderate to large effect size (d = 0.6–1.2) in MDD. All 10 participants completed the required 10 sessions, and 5 participants completed 40 sessions [16]. Our RCT will use 20 sessions of FES, which was well tolerated in research on rTMS for MDD and FES for stroke and spinal cord injury rehabilitation.

A total of 60 participants (30 in the active arm and 30 in the sham arm) is planned to detect a clinically meaningful between-group difference in HAM-D-17 scores, assuming a moderate effect size of 0.5 (Cohen’s d), a two-tailed significance level of 0.05, and 80% power. Accounting for a 15% attrition rate, approximately 51 participants are expected to complete the study, exceeding the recommended minimum sample size (24–50 participants) needed to generate reliable estimates of the standard deviation and correlation of HAM-D-17 scores for future sample size calculations in a definitive trial. Furthermore, a sample size of 60 will allow the anticipated 15% dropout rate to be estimated with an approximate 95% confidence interval margin of error of ±8.4. As the first proof-of-concept RCT of its kind, this trial is designed primarily to detect a signal for the primary outcome, change in HAM-D-17 over time. We recognize that the proposed sample size may not provide high statistical power for some secondary and exploratory outcomes.

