### Outcome measures and data collection

The primary outcomes include changes in depressive symptoms, measured by the HAM-D-17, a validated, semi-structured, clinician-administered interview for assessing the presence and severity of depression. The other primary outcome will assess tolerability and safety based on dropout, data completion, protocol adherence rates, and the frequency and nature of AEs and SAEs. Secondary outcomes include MDD response and remission rates, anxiety, quality of life, and sleep quality. These outcomes will be measured using the 16-Item Quick Inventory of Depressive Symptomatology – Short Form (QIDS-SR-16) [25], Generalized Anxiety Disorder-7 (GAD-7) [26], World Health Organization-5 Well-Being Index (WHO-5) [27], and Pittsburgh Sleep Quality Index (PSQI) [28]. Additional secondary outcomes include response (50% decrease in total HAM-D-17 score) and remission (HAM-D-17 < 7) rates and sustainability of these outcomes for up to 28 days post-stimulation. In addition, facial expressivity during video-recorded emotional recall interviews will be assessed as an exploratory outcome.

An independent assessor will administer the HAM-D-17 and complete the Concomitant Medication Record (CONMED) at baseline, at the end of each week during the randomized intervention period, and at each follow-up visit. Participants will also be queried daily about their experiences and any AEs or SAEs they may encounter. To monitor participant burden, an FES Experience assessment will be conducted at the end of each treatment week through REDCap. All secondary outcomes will be assessed at baseline, at the end of each week during the randomized intervention period, and during follow-up visits using REDCap. Emotional recall interview will be administered at baseline and at the end of each week during the intervention period.

This study will also collect necessary personal health information, including the participant’s name, date of birth, medical records (new or existing) related to psychiatric or medical conditions, current and past medications, surgical implants, and any illnesses or psychiatric procedures that could affect study participation. This information will be obtained from the participant, their physician, or their medical records.

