### Data analysis plan

Baseline demographic and clinical characteristics will be summarized for each treatment group. The primary analyses will be conducted on a modified intention-to-treat (ITT) sample, including all randomized participants who received at least one FES session. The efficacy of FES will be evaluated using ANCOVA to compare changes in HAM-D-17 scores from baseline to the final FES session between the active and sham groups, adjusting for baseline HAM-D-17 score and sex. Correlations between baseline and follow-up HAM-D-17 scores will be analyzed at the participant level. Similar analyses will be conducted for secondary clinical outcomes. Moreover, FES tolerability will be evaluated by summarizing overall dropout rates as counts and percentages. For dichotomous outcomes like remission, response, and AEs, between-group differences will be analyzed using odds ratios with 95% confidence intervals. Blinding effectiveness will be assessed by calculating Bang’s blinding index for rater and participants. Analyses stratified by sex and age will also be performed to explore potential subgroup differences.

Additionally, automated facial behavior analysis software (OpenFace) will be used to quantify Duchenne smile metrics derived from facial Action Units (AUs), including frequency, duration, and average activation intensity. Duchenne smiles will be identified based on the concurrent activation of AU12 (lip corner puller) and AU6 (cheek raiser). Descriptive statistics and group comparisons will be performed to examine differences in genuine smiling between the FES and sham groups. OpenFace is an open-source facial behavior analysis toolkit developed by researchers at the University of Cambridge and Carnegie Mellon University. Using computer vision and machine learning algorithms, it detects facial landmarks (e.g., eye, mouth, and eyebrow positions), estimates head pose, and quantifies facial muscle activity through the Facial Action Coding System (FACS) by identifying the presence and intensity of facial AUs. Participant videos will be processed using OpenFace to extract facial landmark coordinates and AU measurements. The output will consist of CSV files containing numerical facial behavioral data identified only by participants’ study IDs. These de-identified data will subsequently be used for statistical analysis.

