### Success criteria

The success of this study will be assessed quantitatively based on the achievement of its primary and secondary objectives. Success will be evaluated across three domains: efficacy, tolerability, and safety, based on changes in HAM-D-17 scores, participant retention and protocol adherence, and the frequency and nature of AEs and SAEs. Specifically, success will be indicated by a clinically meaningful reduction in HAM-D-17 scores, defined as a reduction of ≥50% from baseline, in the active FES group. Additionally, a statistically significant difference in HAM-D-17 score changes between the active and sham groups will be required. Successful tolerability will be demonstrated by a dropout rate of ≤15% and high adherence to the treatment protocol, with at least 85% of participants completing all scheduled FES sessions.

For safety outcomes, the number, nature, and duration of AEs will be evaluated in both active and sham groups, and no significant differences between groups in AE frequency or severity will indicate successful safety outcomes. Additionally, the sustainability of observed treatment effects will be assessed by analyzing HAM-D-17 response and remission rates, as well as changes in secondary outcomes, including anxiety (GAD-7), quality of life (WHO-5), and sleep quality (PSQI) over the four-week follow-up period. Sustained improvements across these domains in the active group, without significant increases in adverse effects, will further validate the success of the study.

If these success criteria are met, the findings will provide a robust foundation for designing a large-scale, multisite RCT to further evaluate FES for MDD.

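### HAM-D-17 durability over the 28-day follow-up is stated only as response and remission rates, although the full score is rated at every follow-up visit and no between-arm comparison of it after the last session is stated

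*Protocol article*

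**What the plan says.** All places are in the Protocol article.

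- **What is measured.** Under Outcome measures and data collection, an independent assessor gives the HAM-D-17 "at baseline, at the end of each week during the randomized intervention period, and at each follow-up visit". The full score therefore exists for all four follow-up visits.
- **What is compared on the full score.** Under Data analysis plan, the ANCOVA will "compare changes in HAM-D-17 scores from baseline to the final FES session between the active and sham groups, adjusting for baseline HAM-D-17 score and sex". Sample size gives the same endpoint, day 20.
- **What is carried into follow-up.** Outcome measures and data collection lists "response (50% decrease in total HAM-D-17 score) and remission (HAM-D-17 < 7) rates and sustainability of these outcomes for up to 28 days post-stimulation". Success criteria states that "the sustainability of observed treatment effects will be assessed by analyzing HAM-D-17 response and remission rates, as well as changes in secondary outcomes", and names anxiety, quality of life and sleep as examples of those secondary outcomes. The Discussion describes the follow-up in the same terms.
- **How the cuts are compared.** Data analysis plan assigns odds ratios with 95% confidence intervals to remission and response.
- **What hypothesis this serves.** Under Objectives, sustainability over four weeks is part of the secondary objective, and the active arm is expected to improve more than sham.

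**The concern.** Three sections agree on carrying HAM-D-17 into follow-up only as rates. It is a stated choice and not a detail left to another document. Anxiety, quality of life and sleep are followed as changes on their scales, while the primary depression scale is reduced to yes or no at two thresholds.

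A patient who improves by 45% and one who does not improve at all count the same for response. In a trial of 60, that loss of information is expensive. What is at stake is how well the trial can say whether a between-arm HAM-D-17 difference lasts to day 28. That bears on the secondary hypothesis and on the case for a multisite trial.

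Two other uses of follow-up data do not fill the gap. The planned correlation of baseline with follow-up HAM-D-17 is at participant level and does not compare the arms. QIDS-SR-16 is continuous and collected at follow-up, but it is a different, self-reported instrument and cannot show whether the HAM-D-17 difference itself persisted.

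**Working it through.** **Inputs from the article (Sample size).** The plan is "assuming a moderate effect size of 0.5" (Cohen's d), with "a two-tailed significance level of 0.05, and 80% power", 30 per arm, and about 51 completers after 15% attrition.

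**Inputs assumed, because the article does not give them.** The effect d = 0.5 persists in full to follow-up. The sham rate p0 for a cut is 10% to 50%. The correlation r between baseline and follow-up HAM-D-17 is 0 to 0.5.

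**The plan's own figure first.** A two-sided two-sample t-test with d = 0.5, alpha 0.05 and 80% power needs 64 per arm, so 30 per arm does not reproduce. By the normal approximation (63 per arm), covariate adjustment would bring 63 × (1 − r²) down to 30 only at r = √(1 − 30/63) = 0.72. No r is stated. The full-score comparison therefore starts from low power too.

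**Step 1: power on the full score.** Noncentral t with n1 + n2 − 2 degrees of freedom and noncentrality [d/√(1 − r²)] × √(n1·n2/(n1 + n2)).

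- 30/30: √15 = 3.873. Noncentrality is 0.5 × 3.873 = 1.94 (r = 0), 0.524 × 3.873 = 2.03 (r = 0.3) and 0.577 × 3.873 = 2.24 (r = 0.5). Power is 47.8%, 51.5% and 59.4%.
- 25/26: √(650/51) = 3.570. Power is 41.7%, 45.0% and 52.4%.

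**Step 2: power on a cut of the same score.** The active-arm rate is p1 = Φ(Φ⁻¹(p0) + 0.5). Power is by exact enumeration of the two-sided Wald test of the log odds ratio, with 0.5 added to each cell when a cell is zero.

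| Sham rate p0 | Active rate p1 | Power, 30/30 | Power, 25 sham / 26 active |
|---|---|---|---|
| 10% | 21.7% | 16.4% | 9.7% |
| 20% | 36.6% | 26.9% | 23.4% |
| 30% | 49.0% | 31.9% | 26.7% |
| 40% | 59.7% | 34.2% | 29.0% |
| 50% | 69.1% | 32.2% | 28.2% |

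With the 51 completers split 26 sham / 25 active instead, the lowest figure is 13.3% and the highest is again 29.0%.

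**Step 3: the gap.** With 30 per arm the smallest gap is 47.8 − 34.2 = 13.6 points and the largest is 59.4 − 16.4 = 43.0. With 51 completers they are 41.7 − 29.0 = 12.7 and 52.4 − 9.7 = 42.7.

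**Step 4: check on the article's own definitions.** Response is a percentage change and not a plain cut, so both endpoints were also simulated (4,000 replicates per scenario). Assumptions: baseline mean 18, SD 4; follow-up SD 6; sham improvement 5 or 8 points; r 0.3 or 0.5; d = 0.5. Power was 50% to 59% for ANCOVA, 32% to 42% for response and 23% to 32% for remission. A second simulation with other assumed inputs (baseline 20, SD 4.5; follow-up SD 6.5; sham follow-up mean 11 to 15; r 0.3 to 0.7) gave 38% to 76%, 18% to 50% and 5% to 32%. The loss there was 12 to 35 points for response and 16 to 59 for remission. The direction is stable, but the size depends on inputs that the article does not supply.

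**Step 5: a larger effect.** At d = 0.8 with 30 per arm, the unadjusted score comparison has 86% power and the cuts have about 50% to 69% over the same sham rates.

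**The case against.** The strongest reply has five parts.

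- **The sample is small anyway.** A reader might infer that a lasting effect will usually be missed because of the cuts. The figures do not support that as the cause. At d = 0.5 the full-score comparison would itself miss a fully persisting effect in about 41% (100 − 59.4) to 58% (100 − 41.7) of trials. At d = 0.8 the cuts would detect it in about half of trials or more. The uncontrolled pilot is cited as "FES demonstrated a moderate to large effect size (d = 0.6–1.2) in MDD", and Sample size already concedes limited power for some secondary outcomes. This stands, and it limits the claim to a loss of information.
- **No test decides durability.** Success criteria sets no between-arm significance test for follow-up. It speaks of sustained improvement in the active arm, and the odds ratios come with confidence intervals. This also stands. The power figures bear on the between-arm hypothesis in Objectives and on the precision of the odds ratios, not on a pass-or-fail rule.
- **QIDS-SR-16 is there.** It is a continuous depression scale, it is collected at follow-up, and the list of secondary outcomes in Success criteria is open. So it would be wrong to say that depression durability rests on the two cuts alone. It remains true that no continuous comparison of HAM-D-17, the primary instrument, is stated.
- **Follow-up means may be reported anyway.** A reader might infer that the trial will yield no day-28 mean difference or SD. That is an inference from silence. The scores are collected, and nothing prevents their being summarised. What can be said is that no such between-arm estimate is stated.
- **Response and remission are legitimate outcomes.** A 50% reduction is the article's own definition of a clinically meaningful change, and following it over time is coherent. This is a reason to keep the rates, not to leave out the score.

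**Conclusion.** The point holds in a limited form. The article carries HAM-D-17 into follow-up only as response and remission, compared by odds ratios, and states no between-arm comparison of the full score after the final FES session. That wastes information already collected on a stated between-arm hypothesis.

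If d = 0.5 persists, power falls from about 48% to 59% on the score to about 16% to 34% on a cut with 30 per arm, and from about 42% to 52% to about 10% to 29% with 51 completers. These ranges rest on assumed sham rates of 10% to 50% and an assumed baseline correlation of 0 to 0.5. Neither approach has high power at this effect size, so sample size shares the blame. The case for change rests on the consistent direction of the loss and the very low cost of avoiding it, not on any single figure.

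**What to change.** In Outcome measures and data collection, Data analysis plan and Success criteria, add the between-arm difference in HAM-D-17 change from baseline at day 28 post-stimulation as the main sustainability estimate, reported with its 95% CI. Use either the ANCOVA already planned for the primary outcome (baseline HAM-D-17 and sex as covariates) or one repeated-measures model over the weekly and follow-up visits. Keep response and remission rates as supportive results.

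The cost is a change of wording and one more secondary estimate to report. It needs no new data, visits or participants. Recruitment is expected to run until June 2028, so the analysis can still be specified well before results are available.

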## Discussion

To our knowledge, this study is the first RCT to evaluate the efficacy of FES in MDD. This study represents a significant advancement in exploring FES as a therapeutic modality for MDD. It will compare the outcomes of 20 sessions of active versus sham FES, specifically targeting the Duchenne smile muscles. The primary outcomes include efficacy assessed through changes in HAM-D-17 scores, while tolerability and safety will be evaluated through compliance and dropout rates. Secondary outcomes, including HAM-D-17–defined response and remission, anxiety, sleep quality, and quality of life, will also be assessed for up to four weeks after treatment.

Recent work has highlighted fNMES as a method for investigating facial feedback and the growing overlap between neurorehabilitation and psychiatry [29], supporting the investigation of FES as a treatment for MDD. The rationale for this approach is based on the facial feedback hypothesis, which suggests that facial expressions can modulate emotional states through interoceptive and proprioceptive feedback loops [13,14]. By stimulating the zygomaticus major and orbicularis oculi muscles, which are involved in the Duchenne smile, FES may engage these feedback mechanisms and potentially induce neuroplastic changes in neural circuits involved in emotional regulation.

Given the substantial burden of MDD and the limitations of current antidepressant treatments, interest has grown in alternative or adjunctive approaches, including electrical stimulation of facial muscles to modulate mood and emotion and potentially reduce depressive symptoms [14,16,18,30]. Stimulation of the zygomaticus major (smiling muscle) led to more positive emotional reports compared to stimulation of the depressor anguli oris (frowning muscle), even after controlling for discomfort [18]. Pilot studies targeting the muscles involved in Duchenne smiling in healthy individuals and participants with MDD have provided preliminary support for this approach and suggest that FES is well tolerated, with reported AEs limited to mild, transient discomfort [14,16]. This suggests that the emotional effects arise from muscle activation itself rather than sensory stimulation.

Efthimiou et al. (2024) [30] provided further evidence for the facial feedback hypothesis by showing that fNMES of the zygomaticus major increased the likelihood that ambiguous faces expressions would be perceived as happy. The stimulation also affected early (P1, N170) and late (LPP) neural components. These findings indicate that electrical stimulation of facial muscles influences not only emotion recognition but also its underlying neural mechanisms, providing additional evidence for the role of FES in emotion regulation.

Building on this foundation, the current RCT aims to provide rigorous evidence on the efficacy, tolerability, and safety of FES in a larger sample of patients with MDD. If successful, this study will inform the design of large-scale, multisite RCTs to validate these findings and refine the treatment protocol. Additionally, FES holds promise as a self-administered, home-based neurostimulation treatment, offering an accessible and scalable therapy for individuals with MDD.
